## Blood samples, EV characterization, and genotyping

At 24 h (+/- 8 h) after admission and at the three-month follow-up visit, a blood sample consisting of three 3.5 mL citrate collection tubes is drawn by study personnel and centrifuged to yield plasma, which is stored at -80 °C. EV size and concentration will be determined after EV purification using size exclusion chromatography (Izon, Addington, New Zealand) and nanoparticle tracking analysis (NanoSight 300, Malvern Panalytica, Worcestershire, United Kingdom) [37]. Changes in EV surface markers will be studied using the EV Array platform that simultaneous assesses up to 60 EV surface markers [38]. In addition, changes in EV content (microRNA and proteins) will be assessed using nCounter microRNA panels (NanoString, Seattle, WA, USA) and Orbitrap mass spectrometers (Thermo Fisher Scientific, Waltham, MA, USA), respectively.

At the three-month visit, an additional blood sample in a 3 mL EDTA collection tube is drawn and stored at -80 °C without centrifugation. This full-blood sample will undergo DNA extraction and APOE genotyping.

### Cognitive assessments

Post-stroke cognitive function is assessed at three and 12-month follow-up visits using the Repeatable Battery for the Assessment of Neuropsychological Status (RBANS). To reduce learning bias, version A is administered at the three-month visit and version B is administered at the 12-month visit. All assessments are done by trained personnel. Training and scoring are overseen by a neuropsychologist and a neurologist specialized in dementia. All RBANS measures are administered and scored using standard procedures detailed in the Danish manual. The RBANS is a validated repeatable assessment of cognitive function [39, 40]. With 12 subtests it covers the five cognitive domains: immediate memory, visuospatial function, language, attention, and delayed memory. Based on norm data, the RBANS provides sub scores and age-adjusted index scores for each domain and combine them to a total index score.

The Montreal Cognitive Assessment (MoCA) is administered at baseline and at three- and 12-month follow-up. The MoCA is a brief cognitive screening tool validated for post-stroke cognitive impairment [41].

Pre-stroke cognition is assessed by the short version of the Informant Questionnaire on Cognitive Decline in the Elderly (IQCODE). The IQCODE is a validated 16-item questionnaire assessing change in cognition over the course of 10 years [42]. It assesses changes in working, short-term and long-term memory, learning and attention and the ability to perform daily activities. The questionnaire is completed by the nearest relative either in person or by telephone interview. The respondent is asked to rate the change in the patient’s cognitive ability before the AIS or TIA.

### Questionnaires: well-being, depressive symptoms, and physical activity level

Subjective well-being is assessed by the short 5-item World Health Organization Well-Being Index (WHO-5) [43]. Depressive symptoms are measured by the Major Depression Inventory (MDI). The MDI is a 10-item questionnaire covering the symptoms of major depressive disorder [44]. Both the WHO-5 and the MDI are administered at baseline, and at three- and 12-month follow-up. They are answered by patients themselves or with assistance from study personnel.

The Physical Activity Scale for the Elderly (PASE) is used to assess self-reported physical activity level during previous seven days. It is a validated 12-item questionnaire on overall physical activity and it includes work, leisure time-, household- and sports activities to provide a total physical activity score [45]. The PASE is completed by patient interview at baseline and at the follow-up visits.

### Additional assessments

Information about symptom onset, admission time, prior medical history, demographics, alcohol consumption, medication use, admission National Institutes of Health Stroke Scale (NIHSS) score, routine blood chemistry, height, weight, blood pressure, history of smoking, and educational attainment is collected at baseline. Pre-stroke functional ability and post-stroke functional outcome are assessed on the modified Rankin Scale (mRS). Based on information from hospital charts and routine acute MRI, the primary stroke is classified using the Oxfordshire Community Stroke Project classification [46], while the etiological subtype is classified according to the Trial of Org 10,172 in Acute Stroke Treatment (TOAST) criteria [47]. At each follow-up visit, height, weight, and blood pressure are measured. In addition, new clinically verified cardiovascular events are recorded. Cardiovascular events are defined as fatal or non-fatal acute myocardial infarction, AIS, hemorrhagic stroke, or TIA.

### Statistical analysis

The role of capillary dysfunction on PSCI will be assessed by the association between CTH at baseline and PSCI. The primary outcome will be the difference in total RBANS score from three to 12 months follow-up. Secondary outcomes include total RBANS score at 12 months follow-up, difference in MoCA score from three to 12 months follow-up, and MoCA score at 12 months follow-up. All associations will be assessed using linear mixed effects models adjusting for age, sex, educational level, baseline NIHSS, smoking, and diabetes. Analyses will be stratified by APOE genotype (ε4 carriers vs. non-carriers) and pre-stroke cognitive decline (IQCODE > 3.48 vs. IQCODE ≤ 3.48) to assess for effect modification by these factors. Level of cSVD will be assessed as a mediator.

Associations between EV characteristics and cognitive function after stroke will be assessed primarily by exploring differences in EV characteristics at baseline between patients with normal cognition, impaired cognitive function (total RBANS index score 70–85) and reduced cognitive function (total RBANS index score < 70) at 12-month follow-up using analysis of differential expression. Secondary analyses include exploring differences in EV characteristics at baseline among patients with a decline (≥ 6 points) versus patients with no decline in total RBANS score from three to 12 months, between patients with decline (≥ 2 points) versus no decline in MoCA score from three to 12 months follow-up, and between patients above and below MoCA score of 22 and 26 at 12-months follow-up. Analyses will be adjusted for age, sex, educational level, baseline NIHSS, diabetes, and hypertension. In addition, analyses stratified by APOE genotype, pre-stroke cognitive decline, and level of cSVD will be performed.

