### Sample size calculation

A previous study could show a correlation between capillary dysfunction and cognitive status in 32 patients with Alzheimer’s disease [48]. To find a similar effect size in a linear model with 10 predictor variables, a sample size of 71 patients is needed (90% power, significance level 0.05). This calculation was performed using the pwr-package in *R* version 4.3.2 [49]. Previous studies of EV characteristics were able to distinguish between stroke severity, lesion volume and outcome when comparing groups of 21 and 20 stroke patients [50]. A sample size of 100 patients with complete follow-up is therefore considered adequate.

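### The analyses that read 12-month RBANS or MoCA level as post-stroke impairment (including the primary EV comparison) do not adjust for pre-stroke cognition, although IQCODE is collected at baseline

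*Protocol article*

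**What the plan says.** Study objectives (protocol article) frames both primary objectives, for capillary dysfunction and for EVs, in terms of PSCI.

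Statistical analysis then sets these outcomes:

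- **CTH, primary:** "The primary outcome will be the difference in total RBANS score from three to 12 months follow-up".
- **CTH, secondary:** "Secondary outcomes include total RBANS score at 12 months follow-up", together with 12-month MoCA level and MoCA change.
- **EV, primary:** baseline EV characteristics compared across three groups defined by 12-month level, the lowest being "reduced cognitive function (total RBANS index score < 70) at 12-month follow-up using analysis of differential expression".
- **EV, secondary:** groups defined by RBANS or MoCA decline, and groups above and below MoCA 22 and 26 at 12 months.

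The adjustment sets are explicit. For CTH: "All associations will be assessed using linear mixed effects models adjusting for age, sex, educational level, baseline NIHSS, smoking, and diabetes". For EVs: "Analyses will be adjusted for age, sex, educational level, baseline NIHSS, diabetes, and hypertension".

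Pre-stroke cognition is measured. Table 2 schedules the IQCODE at baseline, and Cognitive assessments describes it as a 16-item rating by the nearest relative of change over ten years. It enters the CTH analysis only as a stratifier, "pre-stroke cognitive decline (IQCODE > 3.48 vs. IQCODE ≤ 3.48) to assess for effect modification by these factors". For EVs, the analyses stratified by pre-stroke decline are additional to the main ones.

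Table 1 excludes known dementia, neurodegenerative or other significant brain disease, and pre-stroke mRS above 2. The minimum age is 60.

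**The concern.** A score at 12 months shows how a patient performs then. It does not show when a deficit arose. In a cohort aged 60 or over, screened only for diagnosed disease, some patients will probably have declined before the stroke; the planned stratum above IQCODE 3.48 implies that the authors expect this.

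The article also supplies the link to the exposures. Its sample size section cites a correlation between capillary dysfunction and cognitive status in Alzheimer's disease, and its introduction says that EV characteristics change in disease and with the level of small vessel disease. A patient with early, undiagnosed disease could therefore have altered CTH or EVs and a low 12-month score whatever the stroke did.

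At stake is attribution: an association could be reported as a marker of PSCI when it reflects decline already present on admission. Correction for multiple EV markers would not protect against this, because the association would be real and only its interpretation wrong.

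**Working it through.** **1. Which analyses are reached.** Write each score as a stable pre-stroke component S, a pre-stroke trend g per month that continues, and everything else:

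- Level: Y12 = S + 12g + e12. Both S and g remain in it.
- Change: Y12 − Y3 = (S + 12g + e12) − (S + 3g + e3) = 9g + (e12 − e3). S cancels; only the trend remains.

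The concern therefore reaches the primary EV comparison, the MoCA 22/26 groups and the CTH analyses of 12-month RBANS and MoCA level. It does not reach the primary CTH outcome or the EV decline groups, except through an ongoing trajectory.

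**2. Illustrative size for a level outcome.** The article gives none of the inputs, so they are assumed. Let a be the correlation of CTH with pre-stroke decline and b the absolute correlation of pre-stroke decline with 12-month RBANS, both net of the listed covariates. With no true CTH effect, the spurious partial correlation has size r = a × b. The two-sided 5% test then follows a noncentral t with df = N − 8 (intercept, CTH, six covariates counted as one term each) and δ = √N · r/√(1 − r²).

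| a × b | r | δ at N = 100 | False positives, N = 100 | False positives, N = 71 |
|---|---|---|---|---|
| 0.1 × 0.3 | 0.03 | 0.30 | 6% | 6% |
| 0.2 × 0.5 | 0.10 | 1.01 | 17% | 13% |
| 0.3 × 0.5 | 0.15 | 1.52 | 32% | 24% |
| 0.4 × 0.7 | 0.28 | 2.92 | 82% | 68% |

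The mechanism is the same for a single EV marker, but the figures do not transfer exactly to a three-group comparison.

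**3. Stratifying against adjusting.** A simulation of 400,000 draws used the last three rows of the table, assumed 20% of patients above the IQCODE cut, and took IQCODE reliability as 0.5 or 0.8. Share of the spurious correlation that remained:

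- stratum at or below the cut: about 70–84%
- stratum above the cut: about 43–71%
- continuous IQCODE as a covariate: about 22–59%

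Check for a = 0.2, b = 0.5, reliability 0.5: ab(1 − rel)/√[(1 − a²·rel)(1 − b²·rel)] = 0.05/√(0.98 × 0.875) = 0.054, or 54% of 0.10, as simulated. The upper stratum is also small: 10 to 30 of 100 patients if 10–30% exceed the cut (assumed).

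**4. Cost in sample size.** The article's 71 (10 predictors, 90% power, 5% level) cannot be reproduced from stated inputs, because no effect size is given. Working backwards with the noncentral F test (u = 10, v = 60, λ = f²(u + v + 1)) gives f² = 0.335. Assuming r = 0.50, f² = 0.25/0.75 = 0.333 and N = 71.3, which agrees. At f² = 0.335, an eleventh predictor raises N from 71 to about 74. Power at 100 patients moves from 98.4% to 98.0%. The CTH model lists CTH plus six covariates, so IQCODE may already fit within the ten, depending on coding.

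**The case against.** **The primary CTH outcome is a change.** A reader might infer that none of the main CTH or EV results can separate deficit before the stroke from deficit after it. The article does not support that. Within-patient change from 3 to 12 months removes a stable pre-stroke level. This objection stands, and it confines the point to the level-based analyses.

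**Pre-stroke cognition is not ignored.** Diagnosed dementia and pre-stroke dependency are excluded, and both sets of analyses are stratified by pre-stroke decline, so an estimate in patients with IQCODE at or below 3.48 will exist. This stands in part. The strata serve effect modification for CTH and are extra for EVs, one cut leaves variation within strata, and the main estimates stay unadjusted.

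**IQCODE may lie on the causal path.** The Discussion says that capillary dysfunction contributes to impairment in vascular dementia and Alzheimer's disease. If chronic dysfunction caused the pre-stroke decline, adjustment would remove part of a real effect. That is a reason to show both estimates. It does not rescue the unadjusted one as an estimate for PSCI, since decline before the stroke is not post-stroke impairment. The Discussion also speaks of predicting cognitive function at one year. For prediction alone an unadjusted level is legitimate, but it should then be named as such.

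**The measure is imperfect.** Adjustment left 22–59% of the spurious correlation in the simulation. IQCODE rates change, so it does not capture lifelong low ability. Nor does the article say that every patient will have an informant. All of this stands as a limit on the remedy.

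**Covariate choice belongs in an analysis plan.** Often so, but here the article states both lists in full.

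**Conclusion.** The concern holds for the level-based analyses, chiefly the primary EV comparison by 12-month RBANS group, and also the EV comparisons at MoCA 22 and 26 and the secondary CTH outcomes of 12-month RBANS and MoCA level. Their stated adjustment sets omit pre-stroke cognition, only known disease is excluded, and the planned strata address the problem only partly. The primary CTH outcome is outside the concern unless a pre-stroke trajectory continues through follow-up.

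No figure for the bias follows from the article. The range of 6% to 82% false positives at 100 patients rests wholly on assumed correlations and could be negligible at the low end. A reader might also be tempted to take the share of a norm population scoring below 85 as a measure of the bias. That share describes how common low scores are, not a distortion of any CTH or EV association.

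The change is worth making: it affects one of the two primary analyses and uses a score already scheduled.

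**What to change.** - Add baseline IQCODE as a continuous covariate in the EV differential-expression models and in the CTH models for 12-month RBANS and MoCA level.
- Report the estimate without IQCODE beside each adjusted one, and say that pre-stroke decline may partly reflect chronic capillary dysfunction.
- Keep the 3.48 split for the effect-modification question.
- Describe any level result without this adjustment as cognition after stroke, not as PSCI.
- State how missing IQCODE is handled when no informant is available, for example by imputation with a sensitivity analysis.

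The cost is a short addition to the analysis section, one degree of freedom (about three more patients on the back-solved calculation, within the planned 100) and the work on missing values. Some residual confounding will remain because IQCODE is an imperfect informant rating, and the report should say so.

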### Study procedures and follow-up

Eligible patients are included within the first 24 h of admission. Baseline measurements are carried out within 48 h from admission. In-person follow-up visits are conducted three months (+/- 1 week) and 12 months (+/- 2 weeks) after inclusion. An MRI is performed in extension to the 12-month follow-up visit. If patients decline to participate in the MRI or if they have incurred contraindications to undergo MRI, they are still eligible for the 12-month follow-up visit. In addition, long-term register-based follow-up is planned. It will include follow-up for recurrent stroke, other vascular events, vascular death, and dementia. Study procedures and their timings are listed in Table 2. Figure 1 illustrates anticipated patient inclusion and follow-up.

**Table 2 Tab2:** Study assessments and registrations

Assessment/registration	Baseline	3-month follow-up	12-month follow-up	Long-term follow-up
Demographics	x			
Medical history	x			
Medication use	x			
Admission NIHSS score	x			
Symptom onset and admission time	x			
Acute treatment	x			
Standard blood chemistry at admission	x			
Pre-stroke mRS	x			
IQCODE	x			
Height, weight and BP	x	x	x	
Smoking and alcohol use	x			
MoCA	x	x	x	
PASE	x	x	x	
WHO-5	x	x	x	
MDI	x	x	x	
Educational level	x			
New vascular events		x	x	x
Functional outcome: mRS		x	x	
Stroke classification: TOAST and OSCP		x		
RBANS		x	x	
Blood sample for EVs*	x	x		
Blood sample for APOE genotyping		x		
MRI**	x		x	
Dementia				x

**Blood sample for EVs is drawn 24 h (+/- 8 h) after admission*

***Baseline MRI is performed 24 h (+/- 6 h) after acute MRI on admission*

*NIHSS: National Institutes of Health Stroke Scale, mRS: modified Rankin scale, IQCODE: Informant Questionnaire on Cognitive Decline in the Elderly, BP: blood pressure, MoCA: Montreal Cognitive Assessment, PASE: Physical Activity Scale for the Elderly, WHO-5: World Health Organisation Five Well-Being Index, MDI: Major Depression Inventory, TOAST: trial of Org 10,172 in Acute Stroke Treatment, OSCP: Oxfordshire Community Stroke Project Classification, RBANS: Repeatable Battery for the Assessment of Neuropsychological Status, EVs: extracellular vesicles, APOE: apolipoprotein E, MRI: magnetic resonance imaging*

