### Magnetic resonance imaging

An MRI is performed at 24 h (+/- 6 h) after the acute MRI on admission and again at the 12-month follow-up visit. MRI sequences include T1-weighted 3D images for co-registration, DWI, kurtosis diffusion imaging, 3D fluid-attenuated inversion recovery (FLAIR), susceptibility weighted imaging (SWI), and gradient echo (GRE) and spin echo (SE) perfusion imaging.

White matter hyperintensities, visible on FLAIR images, are semi-automatically outlined [31]. Capillary function is characterized by capillary transit time heterogeneity (CTH), parameterized as the standard deviation of blood transit times within each image voxel using SE perfusion imaging [19, 22, 23]. Finally, grey and white matter microstructural integrity, including dendrite density, axonal density and dispersion, and intra- and extra-axonal water diffusivity are characterized based on DWI and kurtosis diffusion imagning [32–35]. All MRI scans are performed on site with a 3T Siemens Magnetom Vida scanner (Siemens Healthcare, Erlangen, Germany).

The burden of cSVD is assessed on the 24-hour and the 12-month MRI scans. A total cSVD score is calculated based on the STRIVE-1 criteria with local specifications [36]. The cSVD score includes number and location of microbleeds, superficial siderosis, number of lacunes, grade of white matter hyperintensities, grade of global cortical atrophy, and enlarged perivascular spaces. Scoring is independently performed by a trained neurologist and a neuroradiologist. At scoring disagreement, consensus is achieved. Table 3 presents an overview of the used MRI sequences.

**Table 3 Tab3:** MRI sequences and characteristics at 24 h and 12 months

Sequence	Description	Purpose
DWI + ADC	Diffusion Weighted Imaging (DWI) and calculated Apparent Diffusion Coefficient (ADC)	Grey and white matter microstructural integrity, including dendrite density, axonal density and dispersion, and intra- and extra-axonal water diffusivity
Kurtosis	Kurtosis diffusion Imaging	
3D FLAIR	3-Dimensional Fluid-Attenuated Inversion Recovery	White matter hyperintensities, perivascular spaces, and lacunes
3D T1 (MP2RAGE)	3-Dimentional T1- magnetization Prepared Rapid Gradient Echo	Atrophy/cortical thickness
SWI	Susceptibility Weighted Imaging	Microbleeds and superficial siderosis
PWI GRE	Gradient Echo Perfusion Imaging	Capillary transit time heterogeneity
PWI SE	Spin Echo Perfusion Imaging	

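### Acute treatment is recorded and usually precedes the 24-hour CTH and EV measurements, yet it is in neither covariate list; it may confound mainly the analyses of 12-month cognitive level

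*Protocol article*

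**What the plan says.** **Covariates.** The Statistical analysis section gives two lists. For CTH: "All associations will be assessed using linear mixed effects models adjusting for age, sex, educational level, baseline NIHSS, smoking, and diabetes". For EVs: "Analyses will be adjusted for age, sex, educational level, baseline NIHSS, diabetes, and hypertension". Stratification by APOE genotype and pre-stroke cognitive decline is named for both analyses. For EVs, stratification by small vessel disease level is added; for CTH, that factor is a mediator. No adjusted, stratified or sensitivity analysis by acute treatment is named.

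**What is recorded.** Table 2 (Study procedures and follow-up) has a baseline row "Acute treatment". It does not say which treatments it covers. The only NIHSS in the table is "Admission NIHSS score", and Additional assessments lists the same measurement.

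**When the exposures are measured.** For CTH: "An MRI is performed at 24 h (+/- 6 h) after the acute MRI on admission". For EVs: "Blood sample for EVs is drawn 24 h (+/- 8 h) after admission".

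**Outcomes.** The primary CTH outcome is the change in total RBANS from three to 12 months. Secondary CTH outcomes are 12-month RBANS, MoCA change and 12-month MoCA. The primary EV analysis compares three groups defined by the 12-month RBANS index score.

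**The concern.** Patients are admitted within 24 hours of onset to a comprehensive stroke centre, and ischaemic stroke and TIA are pooled, so acute treatment will plausibly differ between them. A variable that comes before the exposure and affects both exposure and outcome is a confounder. The article itself makes the pathway plausible:

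- The Introduction names stroke severity and lesion size as risk factors for post-stroke cognitive impairment, and says EV characteristics may change during acute stroke.
- The imaging section derives CTH from blood transit times.
- The sample size section cites EV studies that separated patients by stroke severity, lesion volume and outcome.

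The only severity covariate is measured at admission. Two patients with the same admission NIHSS, one treated and one not, are handled as exchangeable, although their 24-hour measurements and later cognition may differ because of treatment. A treatment difference could then be read as evidence on capillary dysfunction or as an EV biomarker. A real association could also be masked if treatment moves exposure and outcome in opposing directions.

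**Working it through.** **1. Order of events**

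| Item | Timing in the article | In a covariate list? |
|---|---|---|
| Admission NIHSS | Admission | Both |
| Acute treatment | Baseline registration, time not given | Neither |
| CTH | 24 h ± 6 h after the acute MRI | Exposure |
| EV sample | 24 h ± 8 h after admission | Exposure |
| RBANS, MoCA | Three and 12 months | Outcome |

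That treatment precedes both exposures is an inference from these windows; the article does not state treatment times.

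**2. Level against change.** Let treatment shift cognition by e3 at three months and e12 at 12 months.

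- Effect on a 12-month level outcome: e12.
- Effect on the three-to-12-month change: e12 − e3, which is zero when e12 = e3.

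The primary CTH analysis is confounded by treatment only if treatment alters the course after three months. The primary EV grouping and the 12-month RBANS and MoCA outcomes carry all of e12.

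**3. Size, with every input assumed.** The true association is set to zero. Let p be the share treated, and dC and dY the treatment differences in exposure and outcome, in SD, that remain after the listed covariates.

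Spurious partial r ≈ p(1 − p) × dC × dY

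The false-positive rate is the noncentral F probability with 1 and 100 − 7 − 1 = 92 degrees of freedom at the 5% level.

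| p | dC | dY | Spurious r | False-positive rate, n = 100 |
|---|---|---|---|---|
| any | 0 | any | 0 | 5.0% |
| 0.35 | 0.2 | 0.2 | 0.2275 × 0.04 = 0.009 | 5.1% |
| 0.10 | 0.5 | 0.5 | 0.09 × 0.25 = 0.0225 | 5.5% |
| 0.20 | 0.5 | 0.5 | 0.16 × 0.25 = 0.040 | 6.7% |
| 0.35 | 0.5 | 0.5 | 0.2275 × 0.25 = 0.057 | 8.5% |
| 0.50 | 0.5 | 0.5 | 0.25 × 0.25 = 0.0625 | 9.2% |

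A more extreme case has p = 0.4, dC = 0.8 and dY = 0.5, now in within-group SD. The spurious slope is p(1 − p) dC dY / (1 + p(1 − p) dC²) = 0.096 / 1.1536 = 0.083, against a standard error of about 0.10. Simulation puts the false-positive rate at about 13%.

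These figures use the marginal variance p(1 − p). If the covariates explain a share R² of treatment, it becomes p(1 − p)(1 − R²). With R² = 0.2, for example, 0.0625 falls to 0.0625 × 0.8 = 0.050. The formula describes a linear slope, so it is only a guide to the three-group EV comparison.

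**4. Cost in power.** The article's N = 71 (10 predictors, 90% power, level 0.05) cannot be reproduced, because no effect size is stated. Back-solving with u = 10, v = 71 − 10 − 1 = 60 and noncentrality f²(u + v + 1) gives f² = 0.335 (R = 0.50) for the overall F test. For one coefficient among 10 predictors it gives f² = 0.175 (partial r = 0.39). The named CTH model has 1 + 6 = 7 terms if each counts once. At f² = 0.175:

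| Terms | Power, N = 100 | Power, N = 71 |
|---|---|---|
| 7 (as planned) | 98.0% | 91.3% |
| 8 (treatment, any vs none) | 97.9% | 90.9% |
| 9 (treatment in three categories) | 97.8% | 90.5% |

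All three models stay within the 10 predictors planned for. This is linear-model power, used as an approximation for the mixed model.

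**The case against.** A reader might infer that treatment confounds both primary associations, and to the same degree. The article does not support that. It gives no share treated, type, timing or effect of treatment on CTH, EVs or RBANS, and it never mentions reperfusion; the Table 2 row is generic. Confounding needs treatment to affect both the 24-hour marker and the later outcome given the covariates. If either link is absent, the bias is zero. The primary CTH outcome is a change score, from which a constant effect drops out. These objections stand and limit the point to possible confounding, mainly of level.

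Others stand in part:

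- CTH is defined per voxel with no region named, so a treatment effect confined to the treated territory may not reach the summary used.
- Treatment may shift some EV markers and not others, so the distortion cannot be assumed across all of up to 60 surface markers.
- For purely prognostic use, an EV marker that partly reflects treatment is not invalid. The article's stated aims, however, also concern mechanism.
- Recanalisation is not a listed registration, so the covariate would adjust for treatment given, not for its success.

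A further objection is that an observational study must limit its covariates and that the present set is reasonable. It is, but that does not justify leaving out a collected variable that fits within the planned number of predictors. Nor is this a detail left to an analysis plan, since the article states both lists.

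**Conclusion.** The point holds as a moderate and cheaply corrected weakness. Acute treatment is recorded, will usually precede both exposures, and is missing from both stated adjustment sets, while admission NIHSS cannot stand in for its consequences. The analyses most open to it are the primary EV comparison and the secondary CTH analyses of 12-month RBANS and MoCA. The primary CTH analysis is affected only if treatment changes the course between three and 12 months.

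Under assumed residual effects of up to 0.5 SD on each side and 10% to 50% treated, the false-positive rate for a single association stays between 5.0% and 9.2%. About 13% needs a 0.8 SD shift in the exposure. These are illustrations and not estimates for this cohort.

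**What to change.** In the Statistical analysis section, add acute treatment received, from the existing Table 2 field, to both covariate lists: any against none, or by type if cell sizes allow. At minimum, report a sensitivity analysis with this covariate for the 12-month level analyses. State which treatments the field covers, and note that it records treatment given and not its success.

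The cost is a sentence or two and one or two degrees of freedom, with no new data collection. An analysis restricted to untreated patients is optional and less precise: if 30% to 40% were treated (assumed), 100 patients would leave 60 to 70, below the article's own 71.
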